# Brain‐oscillation-synchronized stimulation to enhance motor recovery in early subacute stroke: a randomized controlled double‐blind three‐ arm parallel‐group exploratory trial comparing personalized, non‐ personalized and sham repetitive transcranial magnetic stimulation (Acronym: BOSS-STROKE)

**DOI:** 10.1186/s12883-023-03235-1

**Published:** 2023-05-25

**Keywords:** Transcranial magnetic stimulation (TMS), Brain oscillation, Brain-state-dependent stimulation, Sensorimotor µ-oscillation, TMS-EEG, Personalized treatment

## Abstract

**Background:**

Stroke is a major cause of death and the most frequent cause of permanent disability in western countries. Repetitive transcranial brain stimulation (rTMS) has been used to enhance neuronal plasticity after stroke, yet with only moderate effect sizes. Here we will apply a highly innovative technology that synchronizes rTMS to specific brain states identified by real-time analysis of electroencephalography.

**Methods:**

One hundred forty-four patients with early subacute ischemic motor stroke will be included in a multicenter 3-arm parallel, randomized, double-blind, standard rTMS and sham rTMS-controlled exploratory trial in Germany. In the experimental condition, rTMS will be synchronized to the trough of the sensorimotor µ-oscillation, a high-excitability state, over ipsilesional motor cortex. In the standard rTMS control condition the identical protocol will be applied, but non-synchronized to the ongoing µ-oscillation. In the sham condition, the same µ-oscillation-synchronized protocol as in experimental condition will be applied, but with ineffective rTMS, using the sham side of an active/placebo TMS coil. The treatment will be performed over five consecutive work days (1,200 pulses per day, 6,000 pulses total). The primary endpoint will be motor performance after the last treatment session as measured by the Fugl-Meyer Assessment Upper Extremity.

**Discussion:**

This study investigates, for the first time, the therapeutic efficacy of personalized, brain-state-dependent rTMS. We hypothesize that synchronization of rTMS with a high-excitability state will lead to significantly stronger improvement of paretic upper extremity motor function than standard or sham rTMS. Positive results may catalyze a paradigm-shift towards personalized brain-state-dependent stimulation therapies.

**Trial registration:**

This study was registered at ClinicalTrials.gov (NCT05600374) on 10–21-2022.

## Introduction

### Background and rationale {6a}

Stroke is a major cause of death and the most frequent cause of permanent disability in western countries, with the absolute number of disease‐adjusted life years associated with stroke rising globally [1, 2]. The standard treatment of patients with debilitating deficits following stroke is task‐specific occupational therapy, e.g., physical therapy. However, many patients spend several weeks and months in rehabilitation clinics and years on conventional therapy modalities with often insufficient functional improvement. Despite improvements in rehabilitation programs, a significant number of patients remain with relevant disability with respect to functional independence and social participation. The success of motor restorative therapy is limited and mainly restricted to behavioral training [3]. The rising number of stroke survivors highly demands innovative therapies for brain restoration in patients suffering from disabling neurological deficits after stroke. Transcranial magnetic stimulation (TMS) therapy provides the possibility of inducing pro‐regenerative plastic changes not only in the stimulated brain tissue but also at the network level [4]. Those changes allow rehabilitation and conventional therapies to be much more effective. The dominant pathophysiological model underlying therapeutic approaches with non‐invasive brain stimulation in stroke is a disbalance in interhemispheric inhibition, where an increase in excitability of the (under‐active and over‐inhibited) ipsilesional hemisphere or a decrease in excitability of the (over‐active and under‐inhibited) contralesional hemisphere is achieved with regular high‐frequency repetitive TMS (rTMS) of the ipsilesional hemisphere or low‐frequency rTMS of the contralesional hemisphere [5, 6]. The neuromodulatory goal of these interventions is t increase cortical excitability of the ipsilesional hemisphere. In terms of therapeutic efficacy, conventional non‐synchronized rTMS has been categorized as “Level B: probable beneficial impact” based on 7 trials [7].

Recent findings indicate that the induction of a long‐term potentiation (LTP)‐like neuromodulatory effect is significantly increased when rTMS is synchronized with real‐time EEG‐defined high‐excitability states (specifically, the trough of the ongoing sensorimotor μ‐oscillation) as repeatedly demonstrated in our work on healthy participants [8–12] and patients with drug‐resistant major depressive disorder [13]. These findings are grounded in the neurophysiology of synaptic plasticity, where a coincidence between excitatory postsynaptic potentials (that can be measured in the EEG) with action potentials (evoked by TMS) underlies the induction of LTP, a principle that is referred to as spike‐timing dependent plasticity [14]. It has also been demonstrated that these oscillations can be accurately targeted in patients after stroke [15].

### Objectives {7}

The BOSS‐STROKE trial is based on the hypothesis that the timing of individual stimuli of the rTMS protocol is critically important for the therapeutic efficacy of rTMS and, specifically, that high‐frequency rTMS needs to be applied during the brief states of high corticospinal excitability to effectively support functional reorganization of brain networks in the early neurorehabilitation phase following stroke. Therefore, the trial will address a critical question: to what extent the strong evidence in basic neuroscience and human neurophysiological experimentation supporting the principle of spike‐timing‐dependent plasticity can be translated into a relevant clinical benefit for the treatment of stroke patients. All trial‐participating patients will receive standard treatment care according to national stroke therapy guidelines. The trial‐specific treatment will be applied additionally. All participating patients in this randomized controlled trial will receive the additional treatment, with one‐third receiving brain-state-synchronized TMS therapy (experimental condition), one‐third receiving non‐synchronized TMS therapy (control condition I) and one‐third receiving sham TMS therapy (control condition II). Regarding diagnostic procedures, all participating patients will be submitted to standard diagnostic procedures in stroke care. Trial‐specific will be the additional performance of a diagnostic EEG (to achieve a higher level of patient safety) and an MRI (to achieve a higher level of diagnostic and treatment precision), which are optional procedures in standard stroke care.

### Trial design {8}

The study is a multicenter randomized controlled double‐blind three‐arm parallel‐group exploratory clinical trial. Patients and raters in the post‐ and the follow‐up assessment will be blinded to the intervention condition the patient receives. A blinding of the medical doctor and/or study personnel conducting the intervention treatment is not possible, since setting‐up and controlling the intervention treatment requires knowledge of the intervention condition.

The study is being conducted as a Medical Device Regulation (MDR) clinical trial. The investigational device (bossdevice, sync2brain GmbH, Tübingen, Germany) is a real‐time digital signal processor that acts as a “brain oscillation state sensor” and consists of hardware and software algorithms. The technology was developed within our group, supported by a transfer of research grant (EXIST) by the German Federal Ministry for Economic Affairs. The device is now being commercialized by a spin-off company, sync2brain GmbH (Tübingen, Germany) under the name “bossdevice”. It is designed to read‐in a real‐time raw data stream from a bio‐signal amplifier (electroencephalography, EEG), to continuously analyze this data and to detect patterns based on oscillations in different frequencies. When such a specific bio‐signal pattern is detected, the device indicates this through a standard output port. This enables a connected device to determine with millisecond accuracy when a specific bio‐signal pattern occurs.

## Methods: participants, interventions, outcomes

### Study setting {9}

All experiments will be performed in a suitable experimental location with a qualified medical doctor according to the MDR prerequisites available on site at the University Hospital. Several national study centers will be participating in the trial. All study centers will be using identical equipment and carry out the study procedures under the same conditions. The list of participating study centers can be obtained from the coordinating investigator.

### Eligibility criteria {10}

#### Subject inclusion criteria

Subjects meeting all of the following criteria will be considered for admission to the trial:▪ Age ≥ 18 years at the time of signing the informed consent.▪ Cerebral ischemia identified by brain imaging (cerebral MRI or CT) occurred 1‐14 days ago.▪ Subject understands and voluntarily signs an informed consent document prior to any study related assessments/procedures.▪ Stroke has resulted in a new arm‐/hand motor deficit with ≤ 50 points in the FMA‐UE.▪ Presence of motor evoked potentials (MEPs) in the paretic hand.If no MEPs can be obtained in the resting muscle, MEP search during isometric contraction of pprox.. 10–20% maximum voluntary contraction (MVC) in the target muscle is to be applied.If no MEPs can be obtained under contraction, MEP search with TMS double pulses (interstimulus interval (ISI) of 15 ms [16] is to be applied.If still no MEPs can be obtained, TMS double pulses are to be applied during isometric contraction.If no MEPs can be obtained, MEP search procedure can be repeated later up to 14 days after stroke onset**▪** The sensorimotor μ‐oscillation is recordable by EEG in the ipsilesional sensorimotor cortex as a power spectral density peak in the alpha frequency range (7-12 Hz) with a signal‐to‐noise ratio of at least 3 dB as compared to the aperiodic fractal background component of the spectrum.**▪** Subject is able to adhere to the study visit schedule and other protocol requirements.

#### Subject exclusion criteria:

Subjects presenting with any of the following criteria will not be included in the trial:**▪** Hemorrhagic stroke (this refers to primary intracerebral hemorrhage only; hemorrhagic transformation of ischemic infarcts is not an exclusion criterion)**▪** Estimated life expectancy < 12 months**▪** Presence of intracranial ferromagnetic metal (extracranial stents ≥10 cm away from the TMS coil are acceptable) in accordance with current safety guidelines [17]**▪** Intraocular metal, cochlear implants**▪** If TMS might interact with sensors of active implants (e.g., intra‐cardiac defibrillators).**▪** If a cranial bone gap affects currents induced by TMS in the brain (such as after craniotomy).**▪** History of seizures or epilepsy.**▪** Treatment intervention can’t be started within 14 days after onset of stroke.**▪** Women during pregnancy and lactation.**▪** Participation in other clinical trials or observation period of competing trials.**▪** Persistent addiction disorder (except for nicotine dependence)**▪** CNS malignoma**▪** If there is any concern by the investigator regarding the safe participation of the subject in the study or for any other reason the investigator considers the subject inappropriate for participation in the study.**▪** The ability to consent in patients who are unable to speak will be assessed on the basis of the NIHSS by an independent physician.

The presence of a cardiac pacemaker is no longer an exclusion criterion, as TMS can be safely operated if at least 20 cm away from the pacemaker [17]. Prior ischemic events are not an exclusion criterion as this would unduly limit the patient population.

### Trial center requirements

The requirements for the participation of a study center in the study are, on the one hand, defined by the legal regulations for the conduct of clinical studies reviewed by the responsible ethics committee of the coordinating center. With regard to study-specific requirements for a study center’s participation in the study, all sites must have long standing expertise with TMS in stroke trials and authority to fully access patients on their Stroke Units for trial recruitment.

The following components are required at the participating centers to perform the intervention:**▪** TMS Stimulator R30 or X100 (MagVenture, Denmark), with EEG filter and coil holder**▪** TMS Active/Placebo coil Cool-B70 A/P (MagVenture, Denmark)**▪** TMS Coil Cooling System (MagVenture, Denmark)**▪** EEG/EMG Amplifier actiCHamp Plus 32 (BrainProducts GmbH, Germany)**▪** TMS-compatible EEG Caps, sizes 54, 56 and 58 cm (EasyCap GmbH, Germany)**▪** Neuronavigation System, e.g., Localite GmbH, Germany**▪** Real-time digital signal processing device and control software (bossdevice, sync2brain GmbH, Tübingen, Germany)**▪** Windows Control PC**▪** Treatment chair and vacuum pillow to position the patient’s head

Funding for equipment not available at some of the study centers was obtained as part of the funding application. The equipment is provided to the centers free of charge via a loan agreement. The real-time signal processing device (bossdevice) is provided free of charge by sync2brain GmbH.

### Who will take informed consent? {26a}

Patients will be checked for eligibility by a study physician after admission due to acute ischemic stroke. Study inclusion is possible from the day of admission. Each eligible patient will be informed about the modalities of the clinical investigation in accordance with the provided patient informed consent (IC). The patient is to be informed both in writing and verbally by the investigator before any study‐specific procedure is performed. The patient will be given sufficient time (i.e., > 24 h) to decide whether to participate in this study and to ask questions concerning this trial. The patient must give consent in writing. The patient and informing physician must each personally date and sign the informed consent form with an integrated declaration on data privacy protection.

### Patients

The target population of this study comprises acute stroke patients with predominantly motor deficits of the upper extremity, who are able to understand and assess the dimension of the study adequately in order to provide informed consent.

In case the study participant is unable to write legibly, but can understand the patient information, the following procedure will be followed: If the study participant is able to speak, oral instead of written consent will be given in the presence of at least one independent witness who was also involved in informing the study participant. The consent given orally will be documented in writing, dated, and signed by the witness. In case the study participant is unable to articulate, the capacity to consent is additionally checked and confirmed by an independent physician. An independent physician will determine the ability of the study participant to give informed consent, based on the following reproducible parameters. These parameters correspond to the score from listed National Institute of Health Stroke Score (NIHSS) items (1. level of consciousness, 2. orientation, 3. following commands, 4. language/aphasia). If the study participant is unable to speak and scores > 1 in at least one subscale of those NIHSS items, the consent cannot be given and the patient cannot participate in the study. Patients with comprehension difficulties who are mentally unable to fully comprehend the consent process are also not allowed to participate in the study.

### Additional consent provisions for collection and use of participant data and biological specimens {26b}

An additional consent form for data collection with a detailed description of the data collection method, information about the patient’s rights and contact information in case of questions is attached to the trial consent form. Biological samples will not be collected.

## Interventions

### Intervention description {11a}

High‐frequency rTMS will be applied to the ipsilesional motor cortex in 400 bursts of 100 Hz triplets with a mean inter‐burst interval of 3 s (20 min treatment duration, 1,200 pulses per day) for five consecutive workdays (6,000 pulses total), followed by 40 min task‐specific hand/arm‐physiotherapy. The physiotherapy will be applied at all study centers according to a uniform standard operating procedure, which is based on standard treatment procedures in stroke care. Stimulation will be provided in a dedicated room by a GCP‐qualified trial physician or trial technician under supervision of a medical doctor. For the primary endpoint, FMA-UE raters will be trained to improve inter-rater reliability.

This trial has one Experimental Condition and the Control Conditions 1 and 2. The three conditions will be randomized 1:1:1. All conditions target the hand representation of the ipsilesional motor cortex.

### Experimental condition (personalized stimulation)

Each 100 Hz triplet is triggered by the real-time digital signal processor, when it detects a EEG‐defined state of high corticospinal excitability (the trough of the ongoing sensorimotor μ‐oscillation). The stimulation intensity will be set to 80% of the resting (or active, see below) motor threshold in the first dorsal interosseus muscle of the paretic hand. A mean interburst interval of 3 s will be targeted by adjusting the power threshold of the μ‐oscillation in the EEG, leading to 20 min treatment duration.

### Control condition 1 (non-personalized stimulation)

The identical rTMS protocol as in Experimental Condition, but 100 Hz triplets will not be synchronized to the ongoing sensorimotor μ‐oscillation.

### Control condition 2 (sham stimulation)

The same protocol as in the Experimental Condition synchronized to the EEG‐defined high excitability state (trough of the ongoing µ-rhythm), but with ineffective rTMS, using the sham side of an active/placebo TMS coil designed for double‐blind clinical trials.

### Explanation for the choice of comparators {6b}

The comparison between the Experimental Condition and Control Condition 1 will reveal to what extent brain‐oscillation‐synchronized rTMS is more effective than non‐brain oscillation‐synchronized but otherwise identical rTMS, i.e., it will address the comparison of primary interest in this trial. The comparison between the Experimental Condition and Control Condition 2 will address the important question to what extent it is the real brain stimulation rather than somatosensory and auditory inputs synchronized to the ongoing brain oscillation that causes the therapeutic effect. Use of a combined active/passive stimulation coil with realistic auditory and somatosensory stimulation enables stimulation that blinds both the patient and the treatment provider to the condition.

The dose (number of stimuli per session, number of sessions) was adopted from previous stroke trials that used high‐frequency rTMS of the ipsilesional motor cortex in early subacute stroke patients [18–21].

### Study visit procedures

#### Screening visit

Screening (V1) will be performed within maximal 14 days prior to first treatment (V2). After having signed the informed consent, patients will undergo all assessments listed below:- Physical and neurological examination and medical history. This includes documentation of the NIHSS, stroke lesion size and site, and major medical complications (e.g. pneumonia).- Clinical Assessments and Tests:◦ FMA‐UE; assessment at screening should be repeated within 3 days prior first treatment (V2), if the screening visit was done earlier◦ Relative grip strength measurement (vigorimeter) of the affected compared to the non‐affected hand. The best of 3 attempts will be documented; assessment at screening should be repeated within 3 days prior first treatment (V2), if the screening visit was done earlier.◦ Stroke‐specific Quality‐of‐Life Scale (SS‐QOL)◦ Modified Rankin Scale Score◦ Barthel Index- EEG measurement (to be repeated within 3 days prior first treatment (V2), if the screening visit was done earlier):◦ Preparation of 32‐channel EEG. Recording of a 5 min resting‐state eyes‐open EEG and subsequent analysis of the signal‐to‐noise (SNR) ratio of the peak of the µ‐oscillation (frequency band 7‐12 Hz) over the ipsilesional sensorimotor area in the C3 (stroke in the left hemisphere) or C4 (stroke in the right hemisphere)‐Hjorth montage.◦ Exclusion of subjects with an insufficient SNR of the sensorimotor µ‐rhythm below 3 dB◦ If applicable a diagnostic EEG measurement can be obtained to screen for abnormal EEG activity (e.g., interictal epileptic discharges) prior to treatment (not relevant for inclusion, sufficient data of one standard EEG can also be obtained from an EEG before screening).- TMS measurement (to be repeated within 3 days prior first treatment (V2), if the screening visit was done earlier):◦ Determination of the TMS hotspot over the hand representation of the ipsilesional motor cortex for eliciting MEPs of maximum amplitude in the first dorsal interosseus muscle of the paretic hand [please cite [22]].◦ Extended MEP search procedure (only in case if no MEPs can be obtained with standard single-pulse TMS in the resting muscle): MEP search during isometric tonic contraction of 10–20% maximum voluntary contraction (MVC) of the first dorsal interosseus muscle of the paretic hand.◦ If no MEPs can be obtained during contraction, MEP search with TMS double pulses (interstimulus interval (ISI) of 15 ms [16]) will be applied in the resting target muscle.◦ If still no MEPs can be obtained, TMS double pulses will be applied during isometric contraction.◦ If no MEPs can be obtained, the MEP search procedure can be repeated later up to 14 days after stroke onset.◦ If still no MEPs can be obtained after 14 days, the patient will be excluded.◦ Otherwise, the resting or active motor threshold in the first dorsal interosseus muscle of the paretic hand will be determined with the method that elicited MEPs. The motor threshold is defined in the resting muscle as the lowest TMS stimulator intensity that results in small MEPs > 50 µV peak-to-peak amplitude in > 5/10 trials. In the active muscle it is the lowest TMS stimulator intensity that results in MEPs > 200 µV in the average of 5 trials [22]. Motor threshold will be expressed as percentage of maximum stimulator output (%MSO).- Neuroimaging session procedures for measurement of anatomical MRI◦ In case the patient has already received a diagnostic MRI scan between onset of stroke and participation in the study, an additional anatomical MRI is required only if the diagnostic MRI scan in not suitable for the navigation system to guide TMS.◦ If the patient has not yet received an MRI between the onset of stroke and participation in the study or the existing MRI is not sufficient, an anatomical MRI (MPRAGE sequence, TE = 2.18 ms, TR = 2300 ms, TI = 1100 ms, flip angle = 9°, 192 slices, voxel size = 1 × 1 × 1 mm, DWI, FLAIR) should be obtained.◦ In the case of MRI contraindications TMS will be applied at the location of the identified hand motor hotspot. Neuronavigation (Localite GmbH) based on MNI‐brain adaption will then be employed to maintain a consistent coil position, orientation and angulation throughout the sessions of a given patient using skull and facial landmarks rather than the anatomical MRI data.- Randomization and Stratification: At the end of the screening visit and after checking all inclusion and exclusion criteria, the eligible study participants will be assigned to their respective treatment by randomization.◦ 1:1:1 randomization by biostatistical center◦ stratification will be applied with regard to:**▪** study center**▪** motor threshold (<60 %; >60 % MSO)

The following procedures will be performed on 5 consecutive working days (V2-V6):Assessment of possible adverse events from previous sessionPreparation of 5‐channel EEGDetermination of TMS hotspot over hand representation of ipsilesional motor cortexDetermination of resting (or active) motor thresholdrTMS intervention (personalized rTMS or non‐personalized rTMS or sham rTMS), 400 bursts of 100 Hz triplets (i.e., 1,200 pulses per session), interburst interval ∼3 s, stimulus intensity 80 % resting (or active) motor threshold.Documentation of session time, parameters and assessment of adverse eventsPhysiotherapy session (40 min) immediately after rTMS intervention

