## Methods: assignment of interventions

### Sequence generation {16a}

Patients will be randomized to one of the three study conditions/arms (1:1:1) and will be stratified according to study center and motor threshold (≤ 60%; > 60%MSO). The biostatistical center produced a randomization list (block randomization) with varying block length and stratified for study center to realize a 1:1:1 randomization. The randomization of each participant will be conducted centrally by the biostatistical centre via electronic interaction. The operator at each center will be responsible to implement the randomized treatment set-up. Patients and raters will be blind to the rTMS condition.

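### The 60% MSO stratum pools resting and active thresholds, so it does not balance the arms on resting-MEP status; record the search step and prespecify an adjustment for it

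*Protocol article*

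**What the plan says.** The Screening visit section of the Protocol article sets out a four-step search for MEPs: single pulse at rest, single pulse under contraction, double pulse at rest, double pulse under contraction. The extended steps are used "only in case if no MEPs can be obtained with standard single-pulse TMS in the resting muscle". The later ones follow in order: "If no MEPs can be obtained during contraction, MEP search with TMS double pulses", and finally "TMS double pulses will be applied during isometric contraction". The inclusion criteria admit patients on the same ladder ("If still no MEPs can be obtained, TMS double pulses are to be applied during isometric contraction").

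The resting or active threshold "will be determined with the method that elicited MEPs". The two criteria differ: more than 50 µV in more than 5 of 10 trials at rest, and more than 200 µV in the average of 5 trials when active. No separate criterion is given for double pulses. Every threshold is expressed in %MSO.

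Allocation is "stratified according to study center and motor threshold" (Sequence generation {16a}), with a single cut at 60% MSO. Neither that section nor the Screening visit section makes the search step a factor, sets a cut per method, or fixes a stratum for patients without a resting MEP.

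**The concern.** A patient reaches the second step only because no single-pulse MEP could be obtained at rest, so that patient has no measurable single-pulse resting threshold. If the active threshold is, say, 55% MSO, the rule puts the patient in the low stratum beside someone whose resting threshold is 55% MSO. The ladder treats the two as different; the stratum does not.

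If resting-MEP status predicts recovery, the arms are left to chance on it. A covariate coded like the stratum would not recover the distinction either. What is at stake is precision and chance balance on one possible prognostic factor.

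**Working it through.** **1. The rule traced for three patients (illustrative values)**

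| Patient | Resting single-pulse MEP | Threshold used | Stratum |
|---|---|---|---|
| A | present | resting, 55% MSO | low |
| B | absent | active, 55% MSO | low |
| C | present | resting, 65% MSO | high |

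A and B share a stratum although they differ in resting-MEP status.

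**2. The plan's own figure (Sample size {14})**

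Inputs: standardized means 0, 0.335 and 0.67; covariate R² 0.2, so residual variance 0.8; 36 per arm; alpha 0.05.

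- Sum of squared deviations from the mean: 2 × 0.335² = 0.22445.
- Noncentrality: 36 × 0.22445 / 0.8 = 10.10, on 2 and 104 degrees of freedom.
- Power: 80.8% (79.5% at 35 per arm). The stated 36 per arm is reproduced.

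**3. Chance imbalance if the stratum does not separate these patients**

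The share without a resting MEP is not in the article, so 15%, 25% and 40% are assumed. The simulation draws three binomial arms of 48. A difference of at least 10 percentage points means at least 5 patients.

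| Assumed share | One given pair of arms | Some pair of the three |
|---|---|---|
| 15% | 20% | 40% |
| 25% | 29% | 54% |
| 40% | 35% | 62% |

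Allocating within strata, with half of these patients in the low stratum and the other patients split evenly (centers ignored), gives nearly the same results: 20/29/35% and 40/55/62%. Under those assumptions the present stratum adds essentially no balance on this factor.

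**4. The same imbalance on the endpoint scale**

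- Residual variance: 12² × 0.8 = 115.2 (SD 12 and R² 0.2 from Sample size {14}).
- Assumed gap after baseline adjustment: 4 to 8 points. A 10-point imbalance shifts an arm contrast by 0.10 × 4 = 0.4 to 0.10 × 8 = 0.8 points.
- Standard error of a pairwise difference: √(2 × 115.2 / 48) = 2.2 with 48 per arm; √(2 × 115.2 / 36) = 2.5 with 36.
- Planned effect: 0.67 × 12 = 8.0 points.

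**5. What adjustment could gain at a 25% share**

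- Share of residual variance = p(1 − p)d² / 115.2.
- d = 4: 0.1875 × 16 / 115.2 = 2.6%. d = 8: 0.1875 × 64 / 115.2 = 10.4%.
- Noncentrality at 36 per arm: 10.10 / (1 − 0.026) = 10.37, power 82%; 10.10 / (1 − 0.104) = 11.27, power 85%.
- Spending two or three further degrees of freedom on the added terms changes these powers by less than 0.1 percentage point.

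**The case against.** The strongest reply is that the article never says what the stratum is for. A reader might infer that it is meant to balance the state of the corticospinal tract, and that it therefore fails or that the randomization is flawed. The documents do not support this. Stimulation intensity is 80% of the resting or active threshold (Experimental condition; treatment visits V2–V6). Stratifying on the threshold actually used therefore balances delivered stimulator output. On that reading, patients with resting and active thresholds of 55% MSO belong together: both are stimulated at 0.80 × 55 = 44% MSO. This stands, and it rules out calling the coding wrong.

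Safeguards also exist. The primary model adjusts for baseline FMA-UE, and the Statistical methods section promises sensitivity analyses for relevant imbalances in known prognostic factors. Both offset part of the problem. Neither names resting-MEP status, and the sensitivity analysis is triggered only by an observed imbalance.

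The percentages in step 3 are what any unstratified factor shows at this sample size. The standard error already reflects that variation, so they do not measure bias. This also stands.

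A reader might further infer that the stratum should be redefined. Moving every patient without a resting MEP above 60% would lower the one-pair chance in step 3 only from about 29% to 24% at a 25% share. It would also give one factor two definitions, since recruitment began in December 2022 (Trial status).

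Finally, the article names only resting and active thresholds. That a threshold may also be a double-pulse value is inferred from its being taken with the method that worked. The point does not depend on it, because pooling resting and active values is enough.

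**Conclusion.** The point holds as a modest weakness in efficiency. The rule pools thresholds obtained in different ways, and nothing else in the design separates patients with and without a resting MEP. Randomization remains valid and type I error is not inflated.

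The size cannot be fixed from the article, which gives neither the share without a resting MEP nor its prognostic weight. With an assumed 25% share and a 4 to 8 point gap, a 10-point imbalance moves a contrast by 0.4 to 0.8 points, against a standard error of 2.2 to 2.5. Adjustment would recover about 3% to 10% of residual variance. With a smaller gap the gain approaches zero. The case for acting rests on the very low cost.

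**What to change.** Leave the randomization stratum as it is. Record for every patient the search step that produced the threshold, including patients already randomized; it is known at screening, so no new measurement is needed.

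Before the code is broken, which is when the Statistical methods section schedules the SAP, prespecify an adjustment for resting-MEP status together with the stratum as randomized. One suitable factor has three levels: resting MEP present with threshold ≤60% MSO, resting MEP present with threshold >60% MSO, and no resting MEP. State whether it enters the primary model or a named sensitivity analysis. It should not depend on an imbalance being seen.

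The cost is one recorded item and a few degrees of freedom. Stimulation, allocation and sample size do not change.
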